### Outcome variables

#### Interview and clinical examination by a clinical nutritionist

Nutritional screening is assessed with the MNA test [10]. The MNA is a widely used and validated tool for detecting malnutrition and its risk in older people. It involves a general assessment of health (questions regarding lifestyle, mobility, and drugs), a dietary assessment (questions regarding type and number of meals), anthropometric measurements, and a subjective self-assessment by the patient. The maximum sum score is 30.0; scores of 24.0–30.0 indicate normal nutritional status, scores of 17.0−23.5 a risk of malnutrition, and scores 0−16.5 malnutrition.

Bodyweight is measured to the nearest 0.1 kg by a beam scale with the subject wearing light clothes and without shoes. Height is measured standing, the head in the Frankfurt Plane position. If the participant is unable to stand, height is measured using indirect demi-span methods. Demi-span is the distance from the midline at the sternal notch to the web between the middle and ring fingers along outstretched arm. After that, height is calculated by a standard formula [11].

Concentrations of plasma albumin and prealbumin are measured according to standard protocols at the Eastern Finland Laboratory Centre ISLAB.

Grip strength of both hands is measured using a Saehan dynamometer (Hydraulic Hand Dynamometer, Saehan Corporation, South Korea) in a sitting position and with an elbow in 90° flexion close to the body. Participants are allowed two maximal efforts for both hands, and the mean value per hand is used.

#### Interview and clinical examination by a dental hygienist

A dental hygienist interviews the participants before carrying out a clinical oral health examination. The interview comprises of questions about the use and opinions of oral health services, self-reported oral health including the need for care, oral health-related quality of life, oral health-related behavior, attitudes towards oral health, and how caregivers assist care recipients in oral care

The dental hygienist conducts clinical examinations using mouth mirrors, WHO periodontal probes, and a headlamp with the participant sitting or lying down [12]. The subjects are first asked about the need for antibiotic prophylaxis in dental care, and if they answer yes, periodontal measurements are excluded. At first, the presence, type, and condition of removable dentures by the jaw are examined outside of the mouth. The need for repair is recorded as yes/no and denture hygiene will be marked as good if no visible plaque or calculus is found. Those wearing removable dentures are asked whether pain exits while using the dentures and if yes what kind of pain. The intraoral examination begins with an examination of the oral mucosa. After that, the number and condition (sound, filled, fractured, decayed, radix, or missing) of the teeth are recorded. The modified Silness and Löe index is used to register plaque [13]. Plaque is measured in the buccal surface of each tooth and registered as no visible plaque, visible plaque in gingival margins, visible plaque also elsewhere and the highest value per tooth is recorded. The number of mobile teeth is recorded after which the periodontal condition of the teeth is examined. Depths of the periodontal pockets are measured on every tooth except wisdom tooth and tooth remnants and registered as no deepened pocket, pocket 4–5 mm, or pocket ≥6 mm. Only the deepest pocket per tooth is recorded. The presence of gingival bleeding on probing is also registered from each tooth except wisdom teeth and recorded as yes, no, or unable to be examined/tooth missing. Possible needs and reasons for acute dental care are recorded, and further instructions to seek care are given to participants.

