## Background

Family caregivers (FCs) take the main responsibility of home care of older people. Family care is currently a common way to organize care of older people even when care recipients’ (CRs) cognitive and functional abilities are severely decreased. FCs are most often spouses in pensionable age with their underlying illnesses [1]. To support FCs, some countries have implemented various forms of formal support, including monetary support and supply of services. Such formal support provided by municipalities can include financial support for Fcs, services, respite care and counseling, and training. In Finland, home care is supported by care’s allowance that includes allowance fees, necessary services for care recipient, leave for FC (3 days per month), and informal care support services [2]. In Finland, 2018, over 47,500 FCs were granted care allowance, of them 65 years or older were 27,591 [3]. Typically, family care is the round-the-clock responsibility of CR covering all basic and instrumental needs. Intensive caregiving correlates with a greater caregiving burden [4] which may affect nutritional and adequate nutrition intake of FCs themselves and impaired capability to prepare nutritional meals for care recipient [5]. Besides, some FCs already suffer from depressive symptoms and psychological stress [6] and significantly lower quality of life at the start of home care [1].

If the nutrition and oral health statuses of family caregivers are not good, older people’s functional ability and general health can decline. This endangers living at home. Therefore, the nationwide goal of shifting the focus of services to outpatient care will not succeed. To achieve this goal, research is needed; for example, how to care for and improve oral health and nutrition for FCs and how these affect their wellbeing, performance, and quality of life. Caring for older people is considered the most economically and humanly sustainable alternative older people care as the number of older people increases, and social services are reduced. The Ministry of Social Affairs and Health in Finland has also stated that the well-being and rehabilitation of FCs should be developed, and for this purpose, a study on the current situation is needed.

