### Study population

Altogether, 250 FCs (Fig. 1) aged 65 years or over, and 250 CRs living in two areas in Eastern Finland will be recruited in this study. The researcher will record the participants, who will be willing to participate in the study and generate the allocation with the computer to assign participants to intervention. Due to the nature of the study, i.e., intervention on nutrition and oral health, blinding is not possible. So, participants and researchers are not blinded because it is impossible considering the design of the study. The FCs who have a caregiver’s allowance granted by municipalities valid on January 1, 2019, are included in the study.

The service managers for older people in Kuopio and Vesanto contact the caregivers first. They inform FCs about the study and ask them to indicate their willingness to participate in the study. Thereafter, the contact details of those interested are communicated to the researchers who are in contact with the volunteers by telephone. After that, they are receiving comprehensive oral and written information about the study and a consent form.

The sample size is based on power calculations on the main evaluation criteria of the intervention, the nutritional status (P-Alb), and the oral hygiene (plaque amount). In this study, power calculation showed that each subgroup required 60 subjects to achieve a statistical power of 0.80 with *α* of 0.05.

At the baseline, all the participants are interviewed and examined at home by a trained nurse, a clinical nutritionist, and a dental hygienist. Nutrition and oral health are measured at the baseline, at 6 months and 12 months. We have no exclusion criteria regarding maximum age, morbidity, or cognition. Subjects with end-of-life care are excluded. If a CR is unable to reply (e.g., in cases of severe cognitive impairment), data collection will be supplemented with an interview of her/his FC.

The control group does not receive the intervention, but they are guided to the health care, if their health status required it or they were at risk of malnutrition or if they need urgent dental care. If a participant is receiving concomitant treatment for, e.g., Alzheimer’s disease, Parkinson’s disease, diabetes, or cardiovascular disease, it will also be continued during the study.

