### Background variables

At the baseline, at 6 months and 12 months, trained nurse collects information about socioeconomic factors, living arrangements, general health status and health-related behavior, functional ability, cognitive status, quality of life, depression symptoms, sense of coherence, morbidity, and medication. Functional ability is assessed with the activities in daily living (ADL) index using the 10-item Barthel Index (scale 0–100), scores [14], 91–99 indicating slight dependency, 61–90 moderate dependency, 21–60 severe dependency and <20 total dependence, and instrumental activities of daily living (IADL) index using the 8-Item Lawton and Brody scale (from 0 to 8), higher scores indicating better functioning [15].

Cognitive status is assessed with the Mini-Mental State Examination (MMSE) on a scale from 0 to 30, scores 18–24 indicating mild cognitive impairment and scores <17 severe cognitive impairment [16]. The 15-item Geriatric Depression Scale (GDS-15) is used to assess depressive symptoms [17]. Quality of life is assessed with the World Health Organization Quality of Life (WHOQOL)–BREF [18] and sense of coherence (SOC) using Antonovsky’s [19] Orientation to Life Questionnaire (SOC-13). The SOC scale comprised of a general factor (SOC) with the three dimensions of comprehensibility (11 items), manageability (10 items), and 8 linesmeaningfulness (8 items).

Comorbidity is determined using a modified version of the Functional Comorbidity Index (FCI) [20]. The nurse records diagnoses (rheumatoid arthritis and other inflammatory connective tissue diseases, osteoporosis, diabetes, chronic asthma or chronic obstructive pulmonary disease (COPD), coronary artery disease, heart failure, myocardial infarction, stroke, depressive disorder, visual impairment, hearing impairment, Parkinson’s disease, multiple sclerosis, or obesity) based on primary care medical records. The investigator is determining the FCI index, where a higher FCI sum score indicates greater comorbidity.

The information on medication is collected using medication lists, packages, and prescriptions. We have used a cut-off of 10 drugs/day as excessive polypharmacy, according to Jyrkkä et al. [21].

All research methods in this study are summarized in Table 1.

**Table 1 Tab1:** Study assessment and timetable

Assessment	Baseline assessments		2-month visit		6-month assessment		12-month assessment	
	FC	CR	FC	CR	FC	CR	FC	CR
Background information	x	x						
GHQ–12	x				x			

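### The antibiotic-prophylaxis screen rests on the care recipient's own answer, so an impaired care recipient who wrongly says no is probed as the rule is written; put the question to the caregiver as well

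*Protocol article*

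**What the plan says.** In the protocol article, the section on the dental hygienist's interview and examination states the safety check: "The subjects are first asked about the need for antibiotic prophylaxis in dental care, and if they answer yes, periodontal measurements are excluded". Without a yes, the hygienist goes on to record pocket depth and bleeding on probing tooth by tooth. Bleeding is "recorded as yes, no, or unable to be examined/tooth missing"; pocket depth is given three depth categories and no such code.

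The Study population section plans for 250 FCs "and 250 CRs living in two areas in Eastern Finland", and states: "We have no exclusion criteria regarding maximum age, morbidity, or cognition". Its provision for CRs who cannot answer for themselves is: "If a CR is unable to reply (e.g., in cases of severe cognitive impairment), data collection will be supplemented with an interview", the interview being with the FC.

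Table 1 schedules the clinical oral examination for both FC and CR at baseline, 6 months and 12 months.

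**The concern.** The article itself treats a need for prophylaxis as a reason not to take periodontal measurements. The errors it can make are unequal. A wrong yes costs some data. A wrong no leads to the procedure that the rule was meant to prevent.

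Self-report is least dependable in people with cognitive impairment, and this trial expects to enrol some. The Background describes family care as common even when CRs' "cognitive and functional abilities are severely decreased", and the Study population section anticipates participants under treatment for Alzheimer's disease. The caregiver interview depends on the CR being unable to answer. It does not depend on whether an answer that is given can be relied on.

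**Working it through.** The article gives no figure to reproduce here, and no calculation of power or error rate applies. The check is to run the stated rules through each combination of answers, then to count what the fix touches.

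**Inputs**
- Screen: the subject's answer, with yes leading to omission (hygienist examination section).
- Caregiver interview: used when the CR cannot answer (Study population).
- Examinations per CR: 3, at the same time points as the FC's (Table 1).
- CRs planned: 250 (Study population).
- Components of the oral examination: Table 1, note b.

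**Step 1: answers about the CR, 3 × 3 = 9 combinations**

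| CR says | FC would say | Stated rule | With the fix |
|---|---|---|---|
| yes | anything (3 combinations) | omit | omit |
| no | yes | **probe** | **omit** |
| no | no | probe | probe |
| no | cannot say | probe | probe |
| cannot say | yes | FC interviewed; omit | omit |
| cannot say | no | FC interviewed; probe | probe |
| cannot say | cannot say | not settled | omit |

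The gap is the second row. The CR has answered, so on a literal reading the caregiver interview is not triggered, and the FC's knowledge is never sought. The fix changes that row and settles the last one. It leaves a CR who says no with an FC who does not know, where probing still goes ahead.

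**Step 2: does another scheduled item catch the error?** Table 1 marks the MMSE for the FC only, so no scheduled cognitive score for the CR would prompt a second question. Nothing in the article links the nurse's information on diagnoses or medication to the prophylaxis screen.

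**Step 3: what the fix touches.** Note b can be read as 9 components: removable dentures, denture hygiene, oral mucosa, number of teeth, condition of teeth, mobile teeth, pocket depth, gingival bleeding and plaque. The fix omits 2 (pocket depth and bleeding), so 9 − 2 = 7 remain. If number and condition of teeth count as one item, it is 2 of 8, with 6 remaining. Mobile teeth stay among those measured because of the stated order: "The number of mobile teeth is recorded after which the periodontal condition of the teeth is examined". Plaque is also scored before the periodontal examination.

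**Step 4: workload.** One extra FC question per CR examination: 1 × 3 = 3 per pair, and 250 × 3 = 750 at most in the trial.

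**Step 5: number at risk.** Harm needs a CR who has teeth, needs prophylaxis, is impaired but responsive, answers wrongly and is not corrected. The article gives no rate for any of these, so no estimate is offered.

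**The case against.** Three objections have weight.

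First, the article does not say that nobody else may be asked. A sensible hygienist may well turn to the FC, and a full protocol or examiner's manual could contain that check. This is fair, and it limits how much the point can claim. Still, the article does more than leave out a detail: it states which answer leads to omission and when the FC is brought in, and followed literally those two rules probe the CR in question.

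Second, the caregiver interview gives severe cognitive impairment as its example, and inability to answer can reasonably be read as inability to answer adequately. On that reading severely impaired CRs are already covered. This largely stands. What remains is the milder case: a CR who converses and gives a confident but wrong no.

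Third, omitting measurements in doubtful cases concentrates missing data in impaired CRs, and the Statistical analyses section warns that missing values clustered in certain groups can distort results. This stands as a cost, confined to pocket depth and bleeding. Neither is a sample-size criterion; those are plasma albumin and plaque.

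A reader might also infer that CR medical records should be searched. The documents do not support building the fix on that. The medication statement, "The information on medication is collected using medication lists, packages, and prescriptions", does not say for whom. The Abstract ties morbidity and medication to the caregivers, and Table 1 marks the comorbidity index for the FC only. It is not clear that such information is held for CRs.

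**Conclusion.** The point holds as a small participant-safety improvement, worth considering. Under the rules as stated, a CR with cognitive impairment who replies but wrongly says no would be probed, at up to three examinations if the error is repeated and the CR has teeth. The number of such CRs cannot be estimated.

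The conclusion rests on two assumptions: that the caregiver interview is used only when a CR gives no usable answer, and that no further check exists in documents not shown.

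A reader might infer more: that impaired CRs in general are unprotected, that staff would not notice impairment, or that the trial's results are compromised. The documents support none of these. Severely impaired CRs are plausibly covered already. Nothing is said about what staff would notice. The screen is the same in all arms and does not govern plaque scoring, so it gives no ground for claiming bias between arms, and power and alpha do not change.

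**What to change.** Add to the hygienist's examination procedure: at each of the three oral examinations, the question on antibiotic prophylaxis is put to the CR and also to the FC on the CR's behalf. If either says yes, or neither can say, pocket depth and bleeding on probing are omitted. Both are then coded as not examinable, using the category that already exists for bleeding and adding it for pocket depth. The rule is applied identically in all arms. The remaining components, including plaque, are measured as planned.

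Count these omissions by arm and include them in the check already planned on whether missing values cluster in certain groups, and report the count alongside the two measures.

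The cost is one question per CR examination, at most 750 in the trial, asked of a participant whose own oral examination falls at the same time points, with all measurements made at home. The downside is a few more missing pocket-depth and bleeding values, mainly among cognitively impaired CRs, in a number that cannot be given in advance. The criteria for needing prophylaxis do not change, and no check of CR medical records is required.

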### Background variables

At the baseline, at 6 months and 12 months, trained nurse collects information about socioeconomic factors, living arrangements, general health status and health-related behavior, functional ability, cognitive status, quality of life, depression symptoms, sense of coherence, morbidity, and medication. Functional ability is assessed with the activities in daily living (ADL) index using the 10-item Barthel Index (scale 0–100), scores [14], 91–99 indicating slight dependency, 61–90 moderate dependency, 21–60 severe dependency and <20 total dependence, and instrumental activities of daily living (IADL) index using the 8-Item Lawton and Brody scale (from 0 to 8), higher scores indicating better functioning [15].

Cognitive status is assessed with the Mini-Mental State Examination (MMSE) on a scale from 0 to 30, scores 18–24 indicating mild cognitive impairment and scores <17 severe cognitive impairment [16]. The 15-item Geriatric Depression Scale (GDS-15) is used to assess depressive symptoms [17]. Quality of life is assessed with the World Health Organization Quality of Life (WHOQOL)–BREF [18] and sense of coherence (SOC) using Antonovsky’s [19] Orientation to Life Questionnaire (SOC-13). The SOC scale comprised of a general factor (SOC) with the three dimensions of comprehensibility (11 items), manageability (10 items), and 8 linesmeaningfulness (8 items).

Comorbidity is determined using a modified version of the Functional Comorbidity Index (FCI) [20]. The nurse records diagnoses (rheumatoid arthritis and other inflammatory connective tissue diseases, osteoporosis, diabetes, chronic asthma or chronic obstructive pulmonary disease (COPD), coronary artery disease, heart failure, myocardial infarction, stroke, depressive disorder, visual impairment, hearing impairment, Parkinson’s disease, multiple sclerosis, or obesity) based on primary care medical records. The investigator is determining the FCI index, where a higher FCI sum score indicates greater comorbidity.

The information on medication is collected using medication lists, packages, and prescriptions. We have used a cut-off of 10 drugs/day as excessive polypharmacy, according to Jyrkkä et al. [21].

All research methods in this study are summarized in Table 1.

**Table 1 Tab1:** Study assessment and timetable

Assessment	Baseline assessments		2-month visit		6-month assessment		12-month assessment	
	FC	CR	FC	CR	FC	CR	FC	CR
Background information	x	x						
GHQ–12	x				x			
ADL	x				x			
IADL	x				x			
MNA	x	x			x	x	x	x
Albumin (g/dL)	x	x			x	x	x	x
Prealbumin (g/dL)	x	x			x	x	x	x
Weight, BMI	x	x			x	x	x	x
Grip strength	x	x			x	x		
SOC	x				x			
WHOQL-BREF	x				x		x	
GDS-15	x				x			
MMSE	x				x			
NPI	x				x			
FCI	x							
Oral health questionnaire^a^	x	x			x	x	x	x
Oral health clinical investigation^b^	x	x			x	x	x	x
Control visit^c^			x					

*FC* family caregiver, *CR* care recipient, *GHQ-12* General Health Guestionnaire-12, *ADL* activities of daily living, *IADL* instrumental activities of daily living, *MNA* Mini Nutritional Assessment, *SOC* sense of coherence, *WHO* Quality of Life Scale-Brief, *GDS-15* Geriatric Depression Scale-15, *MMSE* Mini-Mental State Examination, *NPI* neuropsychiatric inventory

^a^Oral health services, self-reported oral health, need for care, oral health-related quality of life, behavior, attitudes towards oral health, and how caregivers assist care recipients in oral care

^b^Removable dentures, denture hygiene, oral mucosa, number, and condition (sound, filled, fractured, decayed, radix, or missing) of the teeth, number of the mobile teeth, depths of the periodontal pockets, gingival bleeding, and plaque of the teeth

^c^Evaluation the implementation of nutrition and oral care plans and provide follow-up guidance as necessary

### Interventions

#### Nutritional intervention

The tailored nutritional intervention is based on the baseline MNA test and information on plasma albumin concentration and 4-day food records. Based on this evaluation, the nutritionist plans individualized nutritional care together with the FC and possibly also with the CR her/his nurse or relatives, if necessary. The nutritional care plan is developed for those who were at protein-energy malnutrition (PEM) or risk of PEM (MNA score <24 and plasma albumin <36 g/L. Those with insufficient energy or protein intake, or with weight loss, are instructed to increase their intake of energy nutrients by nutrient-dense food items and the number of meals and snacks. To increase energy intake participants are advised to eat more frequent small meals and snacks during the day and to increase the use of vegetable oils in foods and use high-fat vegetable oil-based spreads on bread. To increase protein intake, participants are advised to use dairy products like milk or sour milk as a drink, cheese on bread, and quark, yogurt, curdled milk, and cottage cheese as snacks and to eat daily meals with meat, poultry, fish, or sources of plant protein. The participants are given both daily meals and oral health care written instructions.

